### Study procedure

Figure 2 shows the details of the study’s procedure. This study will be conducted in the local vaccination clinic/point of vaccination where *Cervarix* and its administration service are available and health examination clinics of hospitals where the cervical cancer screening is available. The study subjects will be invited and the ones who have satisfied the inclusion criteria will be enrolled by the field investigators including gynecologists and general practitioners in the aforesaid study sites.

**Fig. 2 Fig2:**
[figure not shown]
Study procedure

Subjects will be stratified into three age groups (9–20 y/o, 21–30 y/o and 31–45 y/o) and divided into exposed and non-exposed groups by vaccination status. The exposed group will include subjects who received 1 or 2 doses of *Cervarix* and the non-exposed group will include subjects who did not receive any doses of HPV vaccine.

During the study period, two visits will be scheduled for all subjects at Month 0 and Month 36, which means the follow-up period will be 3 years. In the first visit, the questionnaire survey will be administrated for all the subjects to obtain the demographic information, sexual history, menstrual and obstetrical histories, etc. For the ones who are eligible for the cervical cancer screening (i, Have sexual debut at the enrollment; ii, no contradiction of screening and iii, are willing to undergo the screening), the type-specific HPV DNA PCR testing will be given within 2 weeks after the enrollment. After 3-years follow-up, the subjects will be called back for the second visit. A questionnaire which measures any changes of behavior during the follow-up period will be performed. Then the second screening with type-specific HPV DNA PCR testing will be given within 2 weeks after the call-back.

At each visit, type-specific HPV DNA PCR testing will be the primary screening approach, and for the ones with unsatisfactory findings (i.e., hr-HPV infection) will be referred to the local abnormal cervical cancer screening results management system for further medical activities (Fig. 1)

By the end of the follow-up period, the prevalence of the HPV infection, cervical disease (e.g., CIN1, CIN2, CIN3, SCC, AIS, etc.) will be described in each birth cohort by their exposure status. If the sample size is sufficient, the effectiveness of *Cervarix* will be assessed as the exploratory objective.

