### Aims

The study aims to evaluate the impact of the AS04 adjuvanted HPV 16/18 vaccine (Brand name: *Cervarix),* for HPV infection and related cervical diseases in real world, with the following objectives:To describe the incidence of HPV 16/18 infection by exposure status, and to evaluate the effectiveness of *Cervarix* on HPV 16/18 infection in birth cohortsTo describe the incidence of cervical lesions or diseases, and other 12 high-risk HPV infection by exposure status in birth cohorts

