### Sample size

Per the previous research, the effectiveness assumptions for *Cervarix* will be 83%, 66%, and 50% for the cohorts of 9–20, 21–30 and 31–45 years of age respectively [23, 24]. The frequency of exposed group vs. non-exposed group will equal to 1: 1 with the level of significance α = 0.05 and statistic power 1-β = 0.8. The statistical analysis was performed on PASS15.0 (Tests for Two Proportions). Considering the loss to follow-up (5% estimated) and subtraction due to the baseline HPV infection and the contamination during follow-up (25% estimated), there will be 30% loss at the end of study. To mitigate this, the targeting recruitment number will be 1/(1–0.3)*100% of the sample size of effectiveness calculation. The detailed variables and calculation of the sample size is demonstrated in the table below (Table 1).

**Table 1 Tab1:** Sample size calculation

Age group(y/o)	Incidence of HPV 16/18 infection	Vaccine effectiveness	Frequency ratio	Exposure group	Non-exposure group	Sample size for effectiveness calculation	Targeting recruitment number
9–20	0.02	0.83	1:1	661	661	1322	1890
21–30	0.02	0.66	1:1	1208	1208	2416	3452
31–45	0.02	0.50	1:1	2371	2371	4742	6776
Total	-	-	-	4240	4240	8480	12,118

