### Endpoints

#### Primary endpoint

Cervical infection with HPV-16 and/or HPV-18 (by PCR), *defined as at least one positive HPV-16 or HPV-18 DNA PCR assay at enrollment (Month 0) or follow-up (Month 36) or any additional screenings during the study period.*

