### Statistical analysis

We will describe the distribution and group differences of the subjects’ general characteristics and the incidence of HPV infection and relevant disease in each age cohort by the exposure status. The categorical data will be described by frequency (proportion) and the Chi-squared test will be performed to show the group difference. The continuous data will be described by mean (standard deviation), and non-normal distribution continuous data will be described by median (quantiles), and then the ANOVA or Wilcoxon rank-sum test will be performed to compare the difference across age groups. Also, the Kaplan–Meier method will be used to draw the survival graph, based on the actual number of cases of each endpoint.

The Logistic Regression will be performed to analyze the impact on HPV 16/18 infection, and HPV 31/33/45 infection in each birth cohort 3 years after vaccination, after adjusting the confounders such as the demographic characteristics, history of sexual behavior, personal behavior history, etc. The vaccine impact will be calculated by using (1-Relative Risk) and its 95% CI.

Stratification analysis will be conducted by frequency of sexual activity, numbers of sexual partners, extramarital sexual activity, family annual income, education level, and cervical cancer screen history. The interaction term between the above factors and HPV vaccination will be introduced into the Logistic regression model, and the differences between the model with interaction term and the model without interaction term will be compared, so as to evaluate the interaction between different factors and HPV vaccination.

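### The HPV 16/18 effectiveness analysis that sizes the whole study is called exploratory and made conditional on an undefined sample size in the Study procedure section

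*Protocol article*

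**What the plan says.** Four parts of the protocol article bear on the status of the effectiveness analysis.

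- **Aims.** The first objective is "To describe the incidence of HPV 16/18 infection by exposure status, and to evaluate the effectiveness of" Cervarix on HPV 16/18 infection in the birth cohorts. It carries no condition and no exploratory label. Cervical infection with HPV 16 or 18 by PCR is also the primary endpoint.
- **Sample size, Table 1.** Each age cohort is sized for a two-proportion comparison of exposed and non-exposed women, "with the level of significance α = 0.05 and statistic power 1-β = 0.8", under assumed effectiveness of 83%, 66% and 50%. The recruitment target of 12,118 is this effectiveness sample size inflated for 30% loss.
- **Statistical analysis.** After an adjusted logistic regression in each birth cohort, "The vaccine impact will be calculated by using (1-Relative Risk) and its 95% CI". No condition is attached.
- **Study procedure, last paragraph.** By the end of follow-up, "the prevalence of the HPV infection, cervical disease" and so on will be described by exposure status. Then: "If the sample size is sufficient, the effectiveness of" Cervarix "will be assessed as the exploratory objective".

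**The concern.** The same estimate cannot be both the powered part of the first objective and an exploratory analysis that may not be carried out. An analysis plan written under this protocol could follow either statement and claim support for it.

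Two things are at stake. First, a reader cannot tell what weight to give the tests at α = 0.05 for which the cohorts were sized. Second, the condition has no criterion and no time point. Exposure status is known throughout, and under Data collection the screening results enter the regional platform in real time. Nothing in the text prevents sufficiency from being judged once outcomes by group can be seen, or from being judged separately by cohort.

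A smaller mismatch sits in the same paragraph: it speaks of prevalence, whereas Aims and Statistical analysis speak of incidence.

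**Working it through.** **1. Is the recruitment target really an effectiveness calculation?**

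Inputs from Sample size and Table 1: incidence in the non-exposed p₁ = 0.02; effectiveness VE = 0.83, 0.66, 0.50; p₂ = 0.02 × (1 − VE) = 0.0034, 0.0068, 0.0100; α = 0.05; power 0.80; ratio 1:1. The number of sides is not stated; two-sided is assumed because it reproduces the table and one-sided does not.

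With p̄ = (p₁ + p₂)/2:

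n per group = [1.96·√(2p̄(1 − p̄)) + 0.842·√(p₁(1 − p₁) + p₂(1 − p₂))]² / (p₁ − p₂)²

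| Cohort | n computed | n in Table 1 | Power at Table 1 n |
|---|---|---|---|
| 9–20 | 658 | 661 | 80.2% |
| 21–30 | 1190 | 1208 | 80.6% |
| 31–45 | 2319 | 2371 | 80.9% |

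Agreement is within 3%. Inflating each group by 1/(1 − 0.3) and rounding up gives 945, 1726 and 3388 per group. Doubled, these are 1890, 3452 and 6776, which sum to 12,118, exactly as in Table 1. The whole target therefore comes from three effectiveness tests at 80% power. No descriptive aim contributes to it.

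**2. How many events are expected at the planned evaluable numbers?**

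Events per cohort = n × p₁ + n × p₂.

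- 9–20: 661 × 0.02 + 661 × 0.0034 = 13.2 + 2.2 ≈ 15.5
- 21–30: 1208 × 0.02 + 1208 × 0.0068 = 24.2 + 8.2 ≈ 32.4
- 31–45: 2371 × 0.02 + 2371 × 0.0100 = 47.4 + 23.7 ≈ 71.1

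These are planning expectations after the 30% loss, not upper limits. With no loss in the cohort aged 9–20 the figure would be 945 × 0.0234 ≈ 22.

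**3. What could count as sufficient?**

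The scenarios below are assumptions for illustration and are not in the article. Power by cohort (9–20, 21–30, 31–45):

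| Scenario | Power |
|---|---|
| 80% of Table 1 n reached | 70.9%, 71.4%, 71.7% |
| 70% reached | 65.1%, 65.6%, 65.9% |
| 50% reached | 51.0%, 51.4%, 51.7% |
| Full n, non-exposed incidence 1% | 50.7%, 51.1%, 51.4% |

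The Study procedure section does not say which of these would pass. The question is a practical one: Feasibility and limitation itself foresees that vaccination of non-exposed women could leave the final analyses underpowered.

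**The case against.** The best defence has four parts.

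*The condition is sample size, not the result.* Evaluable numbers depend on recruitment, loss and contamination, and can be counted without comparing outcomes between groups. This stands. A reader might infer that unfavourable cohorts will be dropped and favourable ones kept, but the article describes no such choice and no cohort-by-cohort decision. A reader might also infer that the decision is fixed at the end of follow-up with outcomes in hand. The phrase about the end of follow-up belongs to the preceding sentence on prevalence, and the conditional sentence has no time point at all. Nor does the section say that prevalence is the sole result to be described.

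*Table 1 supplies a natural benchmark.* Its effectiveness sample sizes of 1322, 2416 and 4742 could define what is sufficient. That is plausible, but Study procedure does not refer to them.

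*A formal threshold belongs in the full protocol or analysis plan.* Agreed: the missing threshold alone would not be a finding in a condensed article. The finding is that the article states two different statuses for one analysis.

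*The sentence may concern other outcomes.* It follows a sentence that covers cervical disease as well as infection, and the second objective (lesions and other high-risk types) is descriptive only. If effectiveness on those outcomes was meant, most of the conflict disappears. The sentence does not limit itself in that way, however, and the preceding one names HPV infection first. On this reading, too, the sentence needs editing.

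**Conclusion.** The conflict holds. Aims, Sample size and Statistical analysis treat HPV 16/18 effectiveness as a planned, powered and unconditional analysis; Study procedure treats it as exploratory and optional. It bears on all three cohort estimates, and most on the cohort aged 9–20, where about 15 expected events make it easiest to call the sample too small.

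The claim is limited to what the wording permits. Omission of the sized analysis after outcomes are known is left open, not announced. No figure in Table 1 is in error. The event counts rest on the article's own 2% incidence and assumed effectiveness. The power scenarios are illustrative and the conclusion does not depend on them.

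**What to change.** 1. In Study procedure, delete the conditional and exploratory sentence as it applies to HPV 16/18 infection.
2. State that effectiveness on HPV 16/18 infection will be estimated and reported with its 95% CI in each of the three age cohorts whatever the final numbers, and that achieved numbers will be shown beside Table 1 where they fall short. A pooled estimate is not needed for this, since Table 1 makes no pooled assumption.
3. If the sentence was meant for cervical disease or other high-risk HPV types, keep it and name those outcomes.
4. Replace prevalence in that paragraph with incidence, to match Aims and Statistical analysis.

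If the sponsor does intend exploratory status for HPV 16/18 effectiveness, then Aims and Sample size must be reworded to match, and the criterion for a sufficient sample must be fixed in advance without sight of outcomes by group. That is the weaker option, because it leaves the study without the analysis that sets its size.

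The cost is a few lines of text. Recruitment, visits and sample size stay as they are. The one downside is that an imprecise cohort estimate must also be reported.

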### Loss of follow-up

For those who were lost, retrieve will be conducted by making phone calls as far as possible. For those who failed to be tracked, the reasons for loss to follow-up will be investigated as far as possible, and the reasons for loss to follow-up will be analyzed. At the same time, the baseline data of lost and non-lost patients, and the ratio of loss to follow-up between exposed and non-exposed groups will be compared to estimate the possible bias.

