### Drop-out criteria

The following criteria should be checked at or right before the follow-up visit. If any become applicable during the study, the subject will withdraw from the study.Pregnancy within the pre-scheduled visiting phase and not eligible for cervical cancer screening.Subjects in the non-exposure group who received any HPV vaccine during the study period.Death due to causes other than cervical cancer.Lost to follow-up (i.e., migrated out the Ningbo city, refusing to respond).

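### The stated attrition-bias check covers only women lost to follow-up and omits withdrawal for HPV vaccination, which only the non-exposed group can have

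*Protocol article*

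**What the plan says.** The Drop-out criteria list four separate reasons for withdrawal:

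- "Pregnancy within the pre-scheduled visiting phase and not eligible for cervical cancer screening"
- "Subjects in the non-exposure group who received any HPV vaccine during the study period"
- "Death due to causes other than cervical cancer"
- "Lost to follow-up (i.e., migrated out the Ningbo city, refusing to respond" (the bracket closes there)

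The Loss of follow-up section plans telephone retrieval, a look at the reasons for loss, a baseline comparison of lost with retained women, and a comparison between exposure groups: "the ratio of loss to follow-up between exposed and non-exposed groups will be compared to estimate the possible bias".

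The Sample size section keeps the same distinction. It allows 5% for loss to follow-up and, as a separate item, "subtraction due to the baseline HPV infection and the contamination during follow-up (25% estimated"). The two add to the 30% used to inflate recruitment.

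The Feasibility and limitation section expects some non-exposed women to be vaccinated, possibly in large numbers. It treats this as a threat to power, and mentions a test-negative design or a post-hoc analysis by vaccine valency in response.

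**The concern.** The article gives the check a purpose, judging bias from attrition, and a scope that does not fit it. The omitted route that matters most is HPV vaccination among controls. It is closed to the exposed group by definition, so wherever it occurs it makes attrition unequal. The women who choose vaccination after enrolment may also differ from those who do not in sexual behaviour, income, education or use of screening, all of which may relate to HPV infection risk.

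If the check is followed as written, a reader who sees similar loss to follow-up in the two groups could conclude that attrition is balanced, although many more controls than exposed women have left. At stake is the comparison of HPV 16/18 infection between groups, which is the effectiveness part of the first objective.

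A smaller point is that comparing baseline tables and loss ratios can signal possible bias but does not yield an estimate of it.

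**Working it through.** **1. The plan's loss figures.** Dividing each per-group size in Table 1 by 1 − 0.3 and rounding up gives:

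- 661/0.7 → 945 per group, 1890 in all
- 1208/0.7 → 1726 per group, 3452 in all
- 2371/0.7 → 3388 per group, 6776 in all

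The total is 12,118, as stated, or 6059 per group. Loss to follow-up at 5% is 0.05 × 6059 ≈ 303 women per group. This is the only planned loss that the check examines.

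**2. What the check would show.** Assume 5% loss to follow-up in both groups, no overlap between reasons, and a share *c* of the non-exposed group withdrawn for vaccination. The article gives no value for *c*, so a range is used.

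| *c* (assumed) | Check as written, exposed vs non-exposed | Loss from both causes, exposed vs non-exposed |
|---|---|---|
| 5% | 5% vs 5% | 5% vs 10% |
| 10% | 5% vs 5% | 5% vs 15% |
| 25% | 5% vs 5% | 5% vs 30% |

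Here *c* is a share of the non-exposed group, not of the pooled 25% allowance. Because contamination falls on one of two equal groups, 10 points of a pooled allowance would be 20% of controls.

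**3. Possible effect on effectiveness.** Further assumptions:

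- The whole non-exposed group would have a risk of 2% if it stayed unvaccinated (the Table 1 incidence).
- True effectiveness is 50% (Table 1, ages 31–45), so the exposed risk is 1%.
- Leavers would have had *r* times the stayers' infection risk, with *r* from 0.5 to 2.
- Loss to follow-up itself causes no bias, and there is no covariate adjustment.

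The stayers' risk *x* solves 0.02 = *c·r·x* + (1 − *c*)·*x*, so *x* = 0.02/(1 − *c* + *c·r*). Observed effectiveness is 1 − 0.01/*x* = 1 − 0.5 × (1 − *c* + *c·r*).

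| *c* | *r* = 0.5 | *r* = 1 | *r* = 2 |
|---|---|---|---|
| 5% | 1 − 0.5 × 0.975 = 51.25% | 50% | 1 − 0.5 × 1.05 = 47.5% |
| 10% | 1 − 0.5 × 0.95 = 52.5% | 50% | 1 − 0.5 × 1.10 = 45% |
| 25% | 1 − 0.5 × 0.875 = 56.25% | 50% | 1 − 0.5 × 1.25 = 37.5% |

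The shift is smaller where effectiveness is higher. At *c* = 25%, a true 66% becomes 1 − 0.34 × 0.875 = 70.25% to 1 − 0.34 × 1.25 = 57.5%. A true 83% becomes 1 − 0.17 × 0.875 = 85.1% to 1 − 0.17 × 1.25 = 78.75%.

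The direction depends on *r*. A comparison limited to loss to follow-up says nothing about *r*, since it does not look at vaccinated controls.

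**The case against.** **This is a condensed article, and a fuller plan may tabulate every withdrawal.** That is possible, and the article does not say that no other comparison will be made. The point does not rest on an omission, though. The article defines the term, applies it to both comparisons and states their purpose. The mismatch is in what is written.

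**The one-sided withdrawal is known and disclosed.** The exclusion criteria screen out controls who intend to be vaccinated, vaccination history is taken from the regional platform, and the limitations section discusses the risk. This stands, so it would be wrong to call the comparison the study's only protection. A between-group ratio for a route closed to one group is also uninformative in itself. The useful comparison is vaccinated controls against retained controls at baseline. The limitations section does not offer it, and the responses it names do not address selection among the controls who remain.

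**The regression already adjusts for demographic, sexual and personal behaviour factors.** This stands in part. Where leaving depends on exposure and those measured factors, the adjusted model handles it. Weighting would use largely the same variables, so it is a sensitivity analysis and not a correction.

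**A stronger reading on size.** A reader might divide 5 by 30 and infer that the check sees one sixth of attrition, or that it looks at the smallest and most balanced part. The documents do not support either. Part of the 25% is baseline HPV infection, which is an exclusion criterion and not attrition. The split is not given, pregnancy and death have no figures, and nothing shows that moving away or refusal is balanced.

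**Conclusion.** The point holds in a limited form. As written, both comparisons leave out pregnancy, death and, most importantly, vaccination among controls, so equal loss to follow-up would not show that attrition is balanced.

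No fraction of missed attrition can be stated. The possible effect is illustrative. With true effectiveness of 50%, non-exposed risk of 2% and leaver risk of 0.5 to 2 times that of stayers, observed effectiveness runs from about 53% to 45% at 10% contamination and from 56% to 38% at 25%. With equal risks it stays at 50%. The contamination levels and the risk ratios are assumptions, and adjustment for measured factors would reduce the shift to the extent that those factors explain it.

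A reader might infer that the effectiveness estimate is biased, or will be presented as free of attrition bias. The documents show neither. Unequal withdrawal is not in itself bias, and the article makes no such claim about its results.

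**What to change.** In the Loss of follow-up section:

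1. Extend both comparisons to every enrolled, baseline-eligible woman without an evaluable follow-up HPV result. Break them down by reason, exposure group and age cohort. Women who stay in the study but are not tested should form their own category, because screening depends on sexual debut, absence of contraindications and willingness.
2. Include the baseline characteristics of controls withdrawn for vaccination against those of retained controls.
3. Say that the comparisons assess possible bias, and drop the claim that they estimate it.
4. Add a sensitivity analysis of effectiveness beside the primary adjusted model. It should keep vaccinated controls' HPV results, positive and negative alike, up to the date of vaccination, and weight by the inverse probability of remaining evaluable, modelled from exposure group and baseline data.

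The questionnaire and the regional platform already supply the baseline factors, vaccination history, call-back status and self-initiated screening, so no new data collection is needed. The cost is extra analysis work and slightly wider intervals. Two limits remain. With visits only at Months 0 and 36, results between baseline and vaccination exist only where a woman had an additional screening. And weighting cannot remove selection on unmeasured factors.

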### Data collection

All the data collected from the surveys and cervical cancer screenings will be documented in the YRHIP, (approval No.: GKYBSZ [2020] No. bc0015; Applicant: Ningbo Yinzhou Center for Disease Control and prevention; Approval time: October 2020).

Once the subject is recruited into the study with signed informed consent form, she will be identified in the YRHIP via her resident identification number and marked as the study subject, and new subpage which contains the study data will be created on her personal file in the YRHIP. The data of the paper-based questionnaire survey will be transcribed into corresponding fields and the cervical cancer screening data will be synchronized with existing healthcare activity page on real-time. Besides the survey and screening data, we’ll also obtain the data of general information, enrollment date, scheduled time of second visit, call-back status, HPV vaccination history, self-initiated cervical cancer screening, cervical related treatment or medication from the YRHIP.

